### Data analysis

The analysis will follow the guidelines of the Consort statement for clustered randomized trials [45] and recommendations for the analysis of clustered randomized trials when presenting and analysing the data.[61,62] The trial statistician will remain blind until the main analyses are complete.

Baseline characteristics of the study population will be summarised separately within each randomised group. Baseline characteristics will also be presented for drop-outs and completers within each treatment group.

### Intention-to-treat sample

The analysis will be performed on the basis of the intention-to-treat principle and will utilise all available follow-up data from all randomised participants. Follow-up data will be collected for all patients whose care-coordinator was randomized independent of whether a care coordinator dropped out or not.

The main statistical analyses will be targeted at estimating the difference in the mean outcomes of Physical and Mental health components of SF36 [43] at 12 and 15 months follow-up observation time point between treatment and control group using a mixed effects model. [63]The outcome variables are assumed to arise from normal distributions. This will be checked and if found to be lacking then appropriate transformations will be applied.

In the linear mixed effects model Physical and Mental health Component scores respectively, at 12 months and 15 months constitute the dependent variables. “Treatment randomisation group, “time (with two levels, 12 and 15 months post-randomization)”, the interaction between “treatment group and time”, “Borough”, and the “baseline values of Physical and Mental Health scores” are the fixed part of the model. “Care coordinator” will be included as a random factor in the model to account for the dependency of the observations within a cluster. “Time” will be entered as a categorical variable.

It is possible that the treatment effects will vary across the care coordinators delivering the interventions. We will therefore also assess an “intervention group x care coordinator” interaction term. A likelihood ratio test of the corresponding variance component and information criteria comparisons will be used to assess if the interactions should be included in the model. Similarly, the interaction between treatment and time will be assessed. Should there be evidence for such an interaction then the relevant terms will be kept in the model. For the final model, the group difference estimates and associated confidence intervals will be reported for 12 and 15 months after randomization.

No *a priori* subgroups were defined in the protocol.

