### Sensitivity of results to missing data

We expect that for a proportion of patients it will not be possible to measure outcome scores at 12 and/ or 15 months and that some data will be missing. The described mixed model will be fitted using maximum likelihood methods that are valid under the missing at random (MAR) assumption.[64] However, this assumption relates to the variables that are included in the model. To allow for a variable predicting “missingness”, this variable needs to be included as either one of the explanatory or dependent variables of the mixed model. We will perform three sensitivity analyses for violations of the assumptions of MAR to assess the sensitivity of the results to missing outcome data:

In the first sensitivity analysis we will use the method of multiple imputations.[64] Data handled using multiple imputation will be imputed 100 or more times, applying a set seed using the ice package in STATA version 11.0 [65]. In this procedure missing data is filled in using other information which has been observed on patients. For our analysis, the imputation model will include all variables which we believe may contain information about the missingness mechanism at 12 and 15 months and must include all variables that will be used in the main analysis model [66]. We account for clustering by including cluster indicators in our imputation model [67]. Each of these completed datasets can then be analysed using the proposed statistical modelling and the estimates from the linear mixed model will be drawn from the average of analysis of each of the completed datasets using Rubin’s Rule [64].

Analysis of data where the outcome is incomplete always requires the untestable assumptions about the missing data that they are missing at random. We, therefore, will perform a second sensitivity analyses to explore the effect of departures (varied over a plausible range) from the assumption of missing at random made in the main analysis as recommended by White et al [68]. For example, to assess for differential drop-out in patients between treatment groups a sensitivity analysis would assume that the cases lost to follow-up have systematically worse outcome than completers and outcome will be worse in treatment group and we will assess the effect of different values on the treatment differences at 12 months.

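### The primary mixed model takes two scores per patient but names only a care-coordinator random effect, so the 12-month and treatment-by-time standard errors are too large and the 15-month estimate is exposed to some missing-at-random dropout

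*Protocol article*

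**What the plan says.** The section 'Intention-to-treat sample' sets out the model. The Physical and Mental component scores "at 12 months and 15 months constitute the dependent variables". The fixed part is listed term by term: treatment group, "time (with two levels, 12 and 15 months post-randomization", their interaction, borough, and the baseline component scores. One random factor is named, care coordinator, which "will be included as a random factor in the model to account for the dependency of the observations within a cluster".

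Two model-building steps follow. On variation of effect between coordinators: "We will therefore also assess an “intervention group x care coordinator” interaction term", for which "A likelihood ratio test of the corresponding variance component and information criteria comparisons will be used". Treatment by time is then assessed in a similar way: "Should there be evidence for such an interaction then the relevant terms will be kept in the model". Group differences at both visits are reported from the model that results.

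The section 'Sensitivity of results to missing data' adds: "The described mixed model will be fitted using maximum likelihood methods that are valid under the missing at random (MAR) assumption". It says that a variable predicting missingness is allowed for when it is among the model's explanatory or dependent variables.

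**The concern.** Two quality-of-life scores from one patient, three months apart, will be correlated well beyond what a shared coordinator produces. A model with only a coordinator effect puts most of the between-patient variance into the residual. Three things are then at stake.

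- The treatment-by-time contrast is a within-patient comparison, so between-patient variance should cancel from it. Here it stays in the standard error. That contrast decides the final model, and a sustained effect at 15 months is one of the article's hypotheses.
- The 12-month contrast, which carries the main hypothesis, also gets too large a standard error while the interaction is in the model.
- Likelihood methods handle dropout that depends on an earlier score by using that score to inform the missing later one. Without a within-patient link, a patient's 12-month score tells the model almost nothing about that patient's 15-month score.

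**Working it through.** **Inputs.** From 'Sample size': SD 12 (mental component), intraclass correlation 0.05, 4 patients per coordinator, 98 coordinators, difference 5 points, 80% power, two-sided 5%. Assumed: 49 coordinators per arm, complete data, SD 12 (a change-score SD) as the SD given baseline, and correlation ρ between a patient's two scores given baseline. The document does not give ρ, so a range is shown. The ratios below do not depend on the SD.

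**The plan's own figures.** Per arm, 91 patients × design effect [1 + 3 × 0.05] = 1.15, × 2 = 209.3, which rounds up to 54 coordinators and 216 patients. Dividing by 0.8 and then 0.7, rounding up to an even number each time, gives 68 and then 98 coordinators, or 392 patients. For the physical component: 63 × 1.15 × 2 = 144.9, giving 38 coordinators and 152 patients, then 48, then 70, or 280 patients. The totals reproduce. (The printed 56 coordinators would give 224 patients; this does not affect the present point.) The calculation is for a single visit, so ρ does not enter it.

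**True variance components at ρ = 0.6.** Total 144. Coordinator 0.05 × 144 = 7.2. Patient 0.6 × 144 − 7.2 = 79.2. Residual 0.4 × 144 = 57.6.

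**What the coordinator-only model estimates** (8 observations per coordinator, 7 within-coordinator degrees of freedom):
- Residual: 57.6 + (6/7) × 79.2 = 125.5.
- Variance of a coordinator mean over both visits: 7.2 + 79.2/4 + 57.6/8 = 34.2. The model preserves this, so its coordinator component is 34.2 − 125.5/8 = 18.5.

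**Contrasts** (variance per coordinator; SE = √(2 × variance/49)):
- 12 months: true 7.2 + 79.2/4 + 57.6/4 = 41.4; model 18.5 + 125.5/4 = 49.9. SE 1.30 against 1.43, ratio 1.10.
- Treatment by time: true 2 × 57.6/4 = 28.8; model 2 × 125.5/4 = 62.7. SE 1.08 against 1.60, ratio 1.48.
- Pooled over visits: 34.2 in both, ratio 1.00.

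**Over the range of ρ:**

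| ρ | SE ratio, 12 months | SE ratio, treatment × time | Rejection rate of a nominal 5% interaction test under no interaction |
|---|---|---|---|
| 0.3 | 1.05 | 1.14 | 2.5% |
| 0.5 | 1.08 | 1.33 | 0.9% |
| 0.6 | 1.10 | 1.48 | 0.4% |
| 0.7 | 1.12 | 1.69 | 0.1% |
| 0.8 | 1.13 | 2.05 | <0.1% |

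The last column is 2 × [1 − Φ(1.96 × ratio)].

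**Power at ρ = 0.6.** A 12-month test with a nominal 80% becomes Φ(2.80 − 1.96 × 1.098) = Φ(0.65) = 74%. Suppose half of the 5-point effect were lost by 15 months, an interaction of 2.5. A correct test detects it with probability Φ(2.5/1.084 − 1.96) = 63%; the planned model does so with Φ(2.5/1.084 − 1.96 × 1.476) = 28%.

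**Simulation, complete data** (REML, 98 × 4 patients, ρ = 0.6, 300 runs). Coordinator only: 12-month model SE 1.42 against an empirical 1.32, coverage 97.0%; interaction 1.60 against 1.07, coverage 99.7%. With a patient effect: 1.30 against 1.32 (94.3%), and 1.08 against 1.07 (95.0%).

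**Simulation, dropout at 15 months depending on the observed 12-month score** (true effect 5 at both visits). In the intervention arm the log-odds of dropout were −1.0 − 1.2 × the standardised 12-month score.

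| Dropout rule | ρ | 15-month bias (coverage), coordinator only | 15-month bias (coverage), with patient effect |
|---|---|---|---|
| Depends on score in one arm only | 0.6 | +1.83 (81%) | +0.01 (96%) |
| Depends on score in one arm only | 0.3 | +0.80 (92%) | 0.00 (95%) |
| Same rule in both arms | 0.6 | −0.41 (97%) | +0.01 (96%) |

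The 12-month bias was between −0.08 and −0.05 throughout, with Monte Carlo errors of 0.07 to 0.08.

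**The case against.** **The article is condensed.** It does not say that care coordinator is the only random factor, and the within-patient structure may be in an analysis plan that is not shown. The remark that dependent variables can carry information on missingness even suggests that the two scores were meant to be linked. This stands in part: nothing shows that the analysis as run will omit a patient term. But the article lists the fixed terms one by one, names one random factor, considers one more at the same level, and then rests its missing-data argument on the model so described. That stated model is the one assessed.

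**The plan's next step may remove the loss of power.** If the effect is equal at both visits, the insensitive test will nearly always drop the interaction, and the reported estimate is the pooled one with a correct standard error. This stands. The 74% applies only when the interaction is kept. The same insensitivity is harmful when the effect truly fades.

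**Stronger readings that the document does not support:**
- A reader might infer that the primary result risks a false positive. For complete, balanced data the standard errors are too large, not too small.
- A reader might infer that validity under missing at random fails outright. It does not. If missingness depends only on arm, baseline or borough, this bias is absent, and with the same dropout rule in both arms it was −0.41. Multiple imputation can also carry the 12-month score into the 15-month imputation, although the imputed data would still be analysed with the same model and its standard errors.
- A reader might infer that the group-by-coordinator term cannot be fitted because each coordinator is in one arm. A separate additional intercept variance would indeed be aliased. Read as a random coefficient on arm, the term gives coordinator variances that differ by arm, and these can be estimated.

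**Conclusion.** The point holds as a fault in the stated model, of limited size at the primary time point. Over an assumed within-patient correlation of 0.3 to 0.8, the model-based standard error is about 5–13% too large at 12 months and 14–105% too large for treatment by time. The direction does not change over that range. The practical cost is a test too insensitive to protect the 15-month question: a real loss of effect could be missed, the interaction dropped, and a pooled estimate reported for both visits.

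The statement on missing at random is too broad for the 15-month estimate. It fails when missingness at 15 months depends on the 12-month score beyond the covariates, and the bias is material mainly when that dependence differs by arm (+0.80 to +1.83 points on a true 5 in the scenarios run). Its size rests on the assumed correlation and dropout strength.

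**What to change.** Add a patient random intercept nested within care coordinator to the model for both component scores. An unstructured within-patient covariance over the two visits is the more general choice, since it also lets the variances differ by visit. Use the same model for the multiply imputed data sets. If the analysis plan already contains such a term, state it alongside the model description.

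As a minor clarification, specify the group-by-coordinator term as coordinator variances that differ by arm.

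The cost is one line of model specification, settled before unblinding. No new data are needed and the sample size calculation is untouched.

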### Objectives

The primary objective is to determine the effectiveness and cost-effectiveness of the addition of an intensive health promotion intervention (IMPACT Therapy), designed to improve physical health and reduce substance use, to usual mental health care delivered by care coordinators (TAU) in people with severe mental illness (SMI) (defined as schizophrenia (ICD-10 code: F20), delusional Disorder (F22.0), schizoaffective disorder (F25), bipolar affective disorder (F31), recurrent depressive disorder (F32), current episode severe with psychotic symptoms (F33.3)).

The main hypothesis is that the addition of IMPACT Therapy (HPI) to TAU will be more effective than TAU alone in improving patients’ quality of life as measured by the Short Form-36, including mental health and physical health subscales [43] on completion of the intervention at 12 months post randomisation. This 12 month period incorporates an initial 3 months post randomisation to train the care coordinators to provide the IMPACT Therapy (HPI) over the following 9 months. We also hypothesise that the effect will be sustained three months after the end of the intervention, at 15 month follow up.

Our secondary hypothesis is that the addition of IMPACT Therapy (HPI) will be more cost-effective than TAU alone in improving health in people with SMI 12 months from baseline and that this cost-effectiveness will be sustained 3 months later at 15-month follow-up.

Subsidiary Hypotheses include

1. TAU plus IMPACT Therapy will reduce waist circumference by at least 1 cm at one year, compared to TAU alone

2. TAU plus IMPACT Therapy will be more effective in reducing weight at one year, compared to TAU alone

3. TAU plus IMPACT Therapy will result in a 50% reduction in proportion of people using cannabis compared to TAU alone.

4. TAU plus IMPACT Therapy will be more effective in reducing symptoms of psychosis compared to TAU alone

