### Sample size

The power analysis is performed for the two subscales measures, Physical and Mental health components of SF-36 Quality of Life scale.[43] We have assumed a common standard deviation of the change scores between baseline and 12 month follow-up of 10 for the Physical component score and 12 for the Mental health component score (based on the QUATRO study [60]), supplemented with further information sought directly from the study team (project reference: QLG4-CT-2001-01734, European Union)) and a cluster size of 4 patients per care coordinator with intraclass correlation of 0.05. Using 80% power, a 5% alpha level and two-tailed assumptions, a sample size of 56 care coordinators and 216 patients are needed to detect a clinical significant difference of 5 points in Mental Health Component change score (Cohen’s d = 0.42), between two groups and a sample size of 38 care coordinators and 152 patients are needed to detect a clinical significant difference of 5 points in Physical Component change score (Cohen’s d = 0.5) between two groups. Assuming a drop-out rate of 20% of the care-coordinators and their patients and an additional patient drop-out rate of 30%, a total sample size of 98 care coordinators and 392 participants are needed for the Mental health score and 70 care coordinators and 280 participants for the Physical health score.

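### Treatment-by-time is both specified in the main model and made conditional on evidence for it, so the data may decide whether the 12-month effect is estimated or replaced by a pooled 12/15-month effect

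*Protocol article*

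**What the plan says.** All references are to the protocol article.

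- **Objectives.** The main hypothesis concerns SF-36 quality of life "on completion of the intervention at 12 months post randomisation". A sustained effect at 15 months is stated as a further hypothesis.
- **Sample size.** Power is calculated for the change from baseline to 12 months.
- **Intention-to-treat sample, model.** The 12- and 15-month scores are joint outcomes in one linear mixed model. Treatment group, categorical time and their interaction are all listed in its fixed part.
- **Intention-to-treat sample, model selection.** A treatment-by-coordinator interaction is to be judged by a likelihood ratio test and information criteria. Treatment-by-time is to be assessed in a similar way, and then: "Should there be evidence for such an interaction then the relevant terms will be kept in the model". No significance level or cut-off is given.
- **Intention-to-treat sample, reporting.** For the final model, "the group difference estimates and associated confidence intervals will be reported for 12 and 15 months after randomization".

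**The concern.** The section gives two answers to one question. The model specification includes treatment-by-time; the selection step includes it only if the data support it.

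This matters because the interaction is what allows the two follow-up times to have different treatment effects. Without it there is a single treatment coefficient, and the 12-month and 15-month group differences are one and the same weighted average. Two things follow if the effects really differ:

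- The estimate labelled 12 months no longer targets the quantity in the main hypothesis. A fading effect pulls it down, and a delayed effect pushes it up.
- Equality at 15 months becomes a feature of the model, although it is what the maintenance hypothesis is about.

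An interval calculated as if the selected model had been fixed in advance also ignores the selection step.

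**Working it through.** **Inputs from the Sample size section.** "Using 80% power, a 5% alpha level and two-tailed assumptions"; a difference of 5 points; standard deviations "of 10 for the Physical component score and 12 for the Mental health component score"; "a cluster size of 4 patients per care coordinator with intraclass correlation of 0.05".

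**Step 1: reproduce the stated sizes.** Design effect = 1 + (4 − 1) × 0.05 = 1.15.

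- Mental: 2 × (1.96 + 0.84)² × 12² / 5² gives 91 per arm (92 by the t-test version). 92 × 1.15 = 105.8, and 105.8 / 4 = 26.45, so 27 clusters per arm. That is 54 clusters and 216 patients. The patient number agrees with the plan; the stated 56 coordinators × 4 would be 224, a separate minor mismatch that does not affect this point.
- Physical: 64 × 1.15 = 73.6, and 73.6 / 4 = 18.4, so 19 clusters per arm, 38 clusters and 152 patients. This agrees.

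A 12-month contrast on its own has about 81.5% power (Mental, 216) or 82.0% (Physical, 152).

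**Step 2: standard errors (Mental, 108 per arm).** For one time point, V = 2 × 12² × 1.15 / 108 = 3.067, so SE = 1.75. With correlation ρ between the 12- and 15-month scores:

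- SE(treatment-by-time) = √(2V(1 − ρ))
- SE(pooled effect) = √(V(1 + ρ)/2)

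The document does not give ρ; 0.3 to 0.8 is assumed. Also assumed are equal variance at both times, complete data, a variance structure that is correctly specified for repeated measures on a patient, and a 5% test.

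Example at ρ = 0.5: SE(treatment-by-time) = 1.75. A fall of 2.5 points gives 2.5 / 1.75 = 1.43, and Φ(1.43 − 1.96) ≈ 0.30, so the term is kept in about 30% of trials.

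**Step 3: apply the rule.** 400,000 normal draws of the two contrasts for each case. If the interaction is significant, the 12-month contrast is reported; otherwise, the average of the two is reported with its own SE.

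| ρ | SE interaction | SE pooled | Term kept (5 then 2.5) | Mean reported 12-month effect | Coverage of 5 | Rejection at 12 months (0 then 2.5) |
|---|---|---|---|---|---|---|
| 0.3 | 2.07 | 1.41 | 23% | 4.3 | 87% | 13% |
| 0.5 | 1.75 | 1.52 | 30% | 4.4 | 89% | 11% |
| 0.7 | 1.36 | 1.61 | 45% | 4.6 | 91% | 9% |
| 0.8 | 1.11 | 1.66 | 62% | 4.7 | 93% | 7% |

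When the term is dropped in the 5-then-2.5 case, the reported effect averages (5 + 2.5)/2 = 3.75. Power in that case is 77% at ρ = 0.5 and 76% at ρ = 0.7, against 81.5% for the fixed 12-month contrast.

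**Step 4: vary the rule and the truth.**

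- An AIC-type rule (equivalent to a test at 0.157) keeps the term in 42% to 80% of trials for 5 then 2.5. At ρ = 0.6 it gives 57% kept, a mean of 4.77 and coverage of 92%, against 36%, 4.49 and 90% for the 5% test.
- Complete loss of effect by 15 months (5 then 0) is detected by a 5% test in 68%, 82%, 96% and 99.5% of trials at ρ = 0.3, 0.5, 0.7 and 0.8.
- Equal effects (5 and 5): the estimate is unbiased, coverage is about 94% to 95%, and power under the rule is about 85% to 93%.

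**The case against.** The strongest reply is that removal is only implied. The interaction is written into the model, estimates are promised at both times, and nothing says outright that the term will be taken out. That is fair as far as it goes, and it is why the point is put as a contradiction. But the sentence on keeping the term has no function if the term always stays. Nor does the promise of two estimates protect the 12-month contrast, since both come from the final model and coincide if the term is gone. A separate analysis plan could settle the matter, but the article states a selection rule; it does not leave the question open.

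A second reply also stands in part: the harm depends on the truth. The Objectives expect a sustained effect. If it is equally large at both times, pooling loses nothing and gains precision.

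Some stronger readings are tempting but not supported:

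- *That the estimand is switched silently.* The selection step is stated openly.
- *That the term goes whenever a test is non-significant.* The article speaks of evidence, names information criteria as well as a likelihood ratio test, and gives no threshold. The 5% level used here is an assumption.
- *That the test is weak in general.* It is weak for partial fading or delay, but not for complete loss of effect when ρ is 0.5 or more.
- *That the damage is much larger because care coordinator is the only random factor named.* Leaving out a patient effect would make the interaction test conservative, but that is a separate question about the random part of the model. The figures above assume the variance is right.
- *That maintenance would be declared confirmed by construction.* The pooled estimate still uses the 15-month data, and the article states no rule for confirming maintenance. What can be said is that a separate 15-month effect would not be estimated.

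**Conclusion.** The point holds as an internal contradiction with a real consequence for the main analysis. On the reading that gives every sentence a function, the data decide whether the 12-month hypothesis is estimated or replaced by a pooled 12/15-month effect under a 12-month label.

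When the true effects differ, the consequence is moderate. In the halved-effect case the average shortfall is about 0.3 to 0.7 of 5 points, with coverage a few points below 95%. In the delayed-effect case the 12-month rejection rate is inflated, which is the more troubling direction because it can produce a false claim on the main hypothesis. An AIC-type rule reduces these errors without removing them. All these sizes rest on the assumed correlation, test level and effect patterns, none of which the document gives. The contradiction itself rests on no assumption.

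**What to change.** State in the analysis section that treatment-by-time stays in the primary model whatever its test or information criteria show. Name the 12-month contrast from that model as the primary estimate and the 15-month contrast as the maintenance estimate. Report the interaction test descriptively, and any pooled effect as supplementary. Delete the conditional sentence as it applies to treatment-by-time, and make the change before the statistician is unblinded.

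Only analysis wording changes. The cost is a wider interval than pooling would give if the effects are in fact equal: at ρ = 0.5, an SE of 1.75 against 1.52. In power terms that is about 81.5% against about 85% to 93% under the selection rule across ρ of 0.3 to 0.8. Since 81.5% is what the stated 216 patients give for a 12-month difference, the planned power is not lost.
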